**Figure 1 F1:**
[figure not shown]
**Flowchart randomization procedure, received care and data collection.** Abbreviations: mEUC = minimally enhanced usual care, UC = usual care.

The intervention group will receive immediate access to “Feel the ViBe” after registration. Considering ethical concerns of withholding an intervention with a possible positive effect on physical and mental health, the control group will be a waiting list condition receiving minimally Enhanced Usual Care (mEUC) for twelve weeks before getting access to the intervention. mEUC is in general defined as non-study care enhanced in minor ways to address methodological or ethical issues. For this RCT mEUC is defined as Usual Care and access to a restricted version of “Feel the ViBe” offering only access to the user profile, consent forms, digital testament, research information, questionnaires and the “ask the expert” function to ask questions in case of emergency. Questions asked by members of the control group will not be answered by the Community Manager, but by one of the members of the Research Team who is not actively involved in the intervention, being author [name]. If help is needed immediately, the participant will be referred to his/her GP (Figure 1).

### Outcomes

The intervention aims to offer peer support, information about family violence and sexual and reproductive health, including relational health, and mental support, in order to reduce PTSD symptoms and improve symptoms of depression and anxiety. Therefore we chose the outcomes measures as follows:

#### Primary outcome measure

•The Impact of Event Scale (IES) will be used to measure PTSD symptoms. The IES is a short set of 15 questions measuring the impact of events and the amount of distress associated with events. It comprises the subscales Intrusion (8 items, mean α = 0.86) and Avoidance (7 items, mean α = 0.82). The IES is measured at t = 0, t = 1, t = 2, t = 3 and t = 4 for both groups [44-46].

•The Depression and Anxiety subscales of the Symptom CheckList-90-R (SCL-90-R DEP and ANX) will be used to measure an improvement in symptoms of depression and anxiety. The SCL-90-R DEP and ANX subscales measure symptoms of depression and anxiety during the previous week on a five-point Likert scale. Both subscales showed good convergent and divergent validity, and high internal consistencies. The SCL-90-R is validated for participants of twelve years old and older. The depression subscale comprises 16 items (α = .90), the anxiety subscale comprises 10 items (α = .88). The SCL-90-R DEP and ANX subscales are measured at t = 0, t = 1, t = 2, t = 3 and t = 4 for both groups [47].

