#### Process evaluation

•The web evaluation questionnaire (WEQ) will contain questions about content, layout, the perceived effectiveness and usefulness of the website, as well as the question to give the website a motivated overall score from 0 to 10, based on their experiences and taking into account their own wishes and needs. The evaluation questionnaire has as goal to identify issues for further improvement of “Feel the ViBe”, to collect possible facilitators and barriers for implementation and to evaluate if the website meets the expectations of the target group. The WEQ is measured twelve weeks after getting access to Feel the ViBe, being t = 2 for the intervention group and t = 4 for the control group.

•“Use” is measured by the collection of quantitative data - being amongst others and duration, visited pages, and visitor numbers - and qualitative data - being forum and chat entries and questions asked to the experts – and is monitored on a continuous base [50,51].

•Demographic variables and data on other (health) care and support received will be collected. At t = 0, participants will also be asked to their expectations, needs and wishes for “Feel the ViBe”.

•After participants have finished all components of the intervention, including all questionnaires, they will be asked if they consent to take part in an interview to discuss in dept their experiences with the intervention.

All questionnaires are provided online and are mandatory to get access to other features. The IES, the SCL-90 and the “Sex-under-25” questionnaire have been administered online before in other studies. Both the general questionnaire and the WEQ have been developed for this trial. Comments and suggestions of test users were incorporated. All the questionnaires have been tested for usability and technical functionality. All responses are being captured automatically.

The primary outcome measures, being the IES and the SCL-90R subscales will be administered four times. This will give us the possibility to determine the optimal duration of the intervention. Participants receive a reminder in their personal menu and via a text message (Figure 1).

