### Sample size

For the calculation of de sample size of the RCT, we searched for studies investigating internet-based methods with the Impact of Event Scale (IES) as a primary outcome measurement [52-55]. We set the confidence interval to 95% and the power to 80%. We calculated the minimal sample sizes using the Cohen’s *d* effect sizes found in these studies. In general, an effect of 0.5 is considered to be a large effect. In the four selected studies, the effect size ranged from 0.7 (leading to 26 participants needed) to 2.0 (4 participants needed), with a mean of 11 and a median of 9 participants needed for each group. Considering the relatively high effect sizes found in these studies and because both the subject of the study and the age of the participants can lead to high drop-out, as seen before in a group of sexually abused adolescents, we aim to include 50 participants for each group at t = 0 [53].

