### Data analysis

Data will be collected for the duration of one year.

First, descriptive statistics of the characteristics of the intervention and the control group will be compared to check whether randomization resulted in similar groups.

The effectiveness of the intervention will be tested with ANOVA of the primary outcome measures. This gives us the opportunity to compare not only the intervention with mEUC (between groups effects), but also to do pre-posttest analysis for all participants (within subjects effects). Data will be analyzed in SPSS. Effect sizes will be expressed in Cohen’s *d* to make data comparable with earlier studies. Data will be analyzed both together and separately for the group 12–17 years old and 18–25 years old.

In e-health trials attrition is typically high and not all participants will use the intervention as intended. A participant will be excluded from analysis if he/she visited the intervention less than five times. His/her entry data (t = 0) will be used to describe baseline characteristics [56].

To interpret the findings, usage data, the WEQ, and the interviews held with the participants after finishing their participation will be analyzed alongside. Qualitative data will be analyzed with qualitative coding [57]. Interview data will be recorded and transcribed. Two researchers will study all transcripts independently, identify themes and establish the definite codes. Consensus will be reached in mutual discussion. Subsequently these outcomes will be formulated and interpreted in the supervising research group for final results. Quotes will be used to underline the results.

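### Three unranked primary outcomes are all tested for effectiveness, with no stated success rule or alpha split, while the sample size rests on the IES alone

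*Protocol article*

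**What the plan says.** The section Primary outcome measure has two bullets. The first gives the IES, for PTSD symptoms. The second begins: "The Depression and Anxiety subscales of the Symptom CheckList-90-R (SCL-90-R DEP and ANX) will be used to measure an improvement"; the improvement meant is in depressive and anxiety symptoms. The section Process evaluation confirms that all three are meant: "The primary outcome measures, being the IES and the SCL-90R subscales". The section Data analysis then says: "The effectiveness of the intervention will be tested with ANOVA of the primary outcome measures". None of these sections ranks the three scales, sets an order of testing, or says whether one or all must succeed.

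The section Sample size looks at one scale only. It draws on four studies of "internet-based methods with the Impact of Event Scale (IES) as a primary outcome measurement", sets a 95% confidence level and 80% power, and reports that "the effect size ranged from 0.7 (leading to 26 participants needed) to 2.0 (4 participants needed" per group. The target is 50 per group, chosen with drop-out in mind. No effect is assumed for either SCL-90-R subscale, and the level is not shared among scales.

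**The concern.** With three primary outcomes, the trial's error rate and power depend on how the three results combine into one conclusion. If any one significant scale supports effectiveness, there are three chances of a false positive, and the overall rate exceeds the 5% implied by the 95% level. If all three scales must be significant, the error rate is safe, but the 80% power calculated for one scale is not the power of the trial. The article does not choose between these rules, and its sample size matches neither. With three unranked primaries, the emphasis can also be chosen after the results are known. The Discussion gives prevention of that kind of selective reporting as a reason for publishing the protocol.

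**Working it through.** **Inputs from the article.** Three primary scales (Primary outcome measure; Process evaluation). Confidence level 95%, power 80%, d = 0.7 giving 26 per group and d = 2.0 giving 4, target 50 per group (Sample size). Allocation 1:1 (Trial design). Drop-out is expected to be high, but no rate is given.

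**Assumptions, not in the article.** The correlation between scales, shown from 0 to 0.9. A 50% loss, used as an illustration. Two-sided tests, unless stated otherwise.

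**1. The article's own figures.** The normal-approximation formula is n per group = 2(z_alpha + z_0.80)² / d², with z_0.80 = 0.842.
- One-sided 5% (z = 1.645): d = 0.7 gives 25.2, so 26; d = 2.0 gives 3.1, so 4. Both match.
- Two-sided 5% (z = 1.960): d = 0.7 gives 32.0, so 33; d = 2.0 gives 3.9, so 4. The 26 does not match.

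The stated figures are therefore reproduced for a single outcome at an undivided 5%, and the 26 only as a one-sided test.

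**2. Any one of three succeeds.** With no true effect and independent scales, the false-positive rate is 1 − 0.95³ = 14.3%. For equally correlated normal statistics (2 million simulated draws each):

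| Assumed correlation | Two-sided 5% each | One-sided 5% each |
|---|---|---|
| 0 | 14.3% | 14.3% |
| 0.3 | 13.6% | 12.9% |
| 0.5 | 12.5% | 11.8% |
| 0.7 | 10.9% | 10.3% |
| 0.9 | 8.4% | 7.9% |

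The rate stays above 5% throughout. The separate analyses by age group are not counted here.

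**3. All three must succeed.** The false-positive rate does not exceed 5%. Power was simulated at two-sided 5% with the same true d assumed on every scale (normal approximation):

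| d, n analysed per group | One scale | All three, correlation 0.5 | All three, correlation 0.7 |
|---|---|---|---|
| 0.7, 50 | 94% | 86% | 88% |
| 0.5, 50 | 71% | 48% | 53% |
| 0.7, 25 (assumed 50% loss) | 70% | 47% | 52% |

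**4. All three stay primary with a split level.** The Bonferroni level is 0.05/3 = 0.0167, two-sided z = 2.394. At d = 0.7, n = 2(2.394 + 0.842)² / 0.49 = 42.7, so 43 per group (the t-test gives 44.2, so 45). At d = 0.5 the formula gives 83.8, so 84. Power of a two-sided t-test on one scale:

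| d, n analysed per group | At 0.05 | At 0.0167 |
|---|---|---|
| 0.7, 50 | 93% | 85% |
| 0.7, 25 (assumed 50% loss) | 68% | 50% |
| 0.5, 50 | 70% | 53% |

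Holm is never less powerful than Bonferroni, so the last column is a floor for Holm.

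**The case against.** The strongest reply is that the article never says the tests are uncorrected. It sets no alpha for the effectiveness tests, and an adjustment method is something an unseen analysis plan may supply. This stands as far as it goes: the absence of correction is inferred from one undivided level, and the inflation applies only under an any-one rule that the article does not state. It does not remove the point. The number and standing of the primary outcomes, and the level at which the trial was sized, are protocol matters, and they are fixed here as three equals sized as one.

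A second reply is that the intervention aims at PTSD symptoms, depression and anxiety, so three primary outcomes are a deliberate choice. That is legitimate, but it then needs a success rule.

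A third is that 50 per group is generous. This stands in part: 50 still covers the Bonferroni level at d = 0.7 if losses are small. It does not at d = 0.5, or if about half are lost.

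A reader might also infer that significance at any follow-up wave would count, so that the waves multiply the tests further. The article does not support this. Its Data analysis section describes ANOVA with between-group and within-subject effects, which reads naturally as one repeated-measures analysis per scale. The stated purpose of the repeated waves is to find the optimal duration. Controls also gain access after twelve weeks, so the later waves are not comparisons with the control condition.

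**Conclusion.** The point holds in this form: three unranked primary outcomes, each tested for effectiveness, with sizing on one of them at a single undivided level and no rule for combining them. Under any-one success at two-sided 5% each, the false-positive rate is about 8% to 14%, depending on a correlation between scales that the article does not give. Under all-must-succeed there is no inflation, and the loss is in power. The documents do not show that the tests will certainly go uncorrected, or that power on the SCL-90-R subscales is inadequate, since no effect is assumed for them. This should be corrected, but it does not invalidate the design.

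**What to change.** Name the IES total score at t = 2 as the single primary outcome. This matches the scale used for sizing, and t = 2 (twelve weeks) is the last wave before controls gain access. Make SCL-90-R DEP and ANX key secondary outcomes, tested in a stated fixed order at 5%, each only if the one before it is significant and starting only if the IES is. This keeps the overall rate at 5% and needs no new data or participants. The cost is that depression and anxiety lose primary status and cannot support a confirmatory claim if the IES fails.

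If all three stay primary, state that success on any one counts, apply Holm at an overall 5%, and report the power cost shown above (at d = 0.7: 93% to 85% with 50 per group, 68% to 50% with 25 analysed). If instead all three must succeed, say so and base the sample size on that rule, with an assumed effect for each scale. In every case, state whether the tests are one- or two-sided.

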#### Secondary outcome measures

•Routine Outcome Measurement (ROM) will be used to follow participants from session to session. On every login, participants will see a pop-up asking them how they would grade their mood at that precise moment on a visual analogue scale using smiley’s. After logging out they will receive a pop-up asking the same question. The scores and differences in scores before and after the session are analyzed to find any direct effects of visiting the website [48].

•An adapted version of the “Seks onder je 25e” (Sex-under-25) questionnaire will be used to measure an increase in knowledge on sexual and reproductive health, including relational health and a decrease of sexual risk taking behaviour. This validated questionnaire is used in a survey in the Netherlands every few years amongst adolescents twelve to twenty-five. In 2011 the questionnaire was filled out online by a representative sample of 10.000 youngsters. It discusses sexual, reproductive and relational health in a broad way handling for example topics as sexual education, ‘the first time’, negative experiences, and contraception. Using this questionnaire will enable us to compare health status of the target group with a population sample. The “Seks onder je 25e” (Sex-under-25) questionnaire is measured at t = 0, t = 2 and t = 4 for both groups [49].

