**Methods/design:**

This study is a randomized controlled trial using the method of minimization to randomize the participants in two parallel groups with a 1:1 allocation ratio, being an intervention group, having access to “Feel the ViBe” and usual care (UC), and a control group, having access to minimally enhanced usual care (mEUC) followed by access to the intervention after twelve weeks. Outcomes are measured with questionnaires on PTSD symptoms, mental health and sexual and reproductive health. Routine Outcome Measurement (ROM) will be used to measure a direct effect of participating in the intervention. Data from a web evaluation questionnaire (WEQ), user statistics and qualitative analysis of online data will be used to support the findings. To compare results Cohen’s d effect sizes will be used.

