### Intervention

“Feel the ViBe” is an internet-based intervention without face-to-face elements. “Feel the ViBe” is based on the theory that self-help, by means of peer-support and information, is an effective way of healthcare for the majority of the target group, while a minority will need further, face-to-face, help. The intervention is available online via http://www.feel-the-vibe.nl and consists of several elements, being amongst others a forum, a chat function, information, and a “ask the expert” function (Table 1). More information can be obtained by contacting the corresponding author. During the RCT the intervention will be ‘frozen’: no changes will be made to the intervention, except for changes due to unexpected events, such as bug fixes. These and other unexpected events, such as system downtimes, will be registered.

**Table 1 T1:** "Feel the ViBe" elements

**Element**	**Extra information**	**Restrictions**
General information on exposure to family violence	Information by age (under-twelve, 12–17, 18–25 and parents) and by subject.	No restrictions
Research information & disclaimer	Information for participants and parents about research, safety and privacy.	No restrictions
Information on sponsoring	Homepage, bottom left.	No restrictions
Contact page	Option to register or ask questions to the community manager or researchers.	No restrictions
News page	Twitter newsfeed included. The news page states important information for participants such as major bug fixes, changes in content and scheduled maintenance.	No restrictions
Emergency exit	A button on every page directing participants to http://www.google.nl.	No restrictions
Electronic consent for participants	Consent is necessary to get access to other elements behind login	Available after first login. *Element will be removed after trial.*
Electronic consent for parents	Consent is necessary for participants under 16 years old to get access to other elements behind login	Accessible by e-mail link with a code. *Element will be removed after trial.*

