Routine Outcome Measurement (ROM)	Directly after login and after logout a popup appears to the participant requesting to state their mood by means of smiley’s. The smiley is optionally visible in the profile as avatar.	Login needed
Facts & Figures	In a twelve-week cycle, participants receive a one-sentence fact of figure about family violence, sexual health, or reproductive health every day on their mobile or by e-mail.	Questionnaires finished

Overview of the elements of the internet-based self-support method “Feel the ViBe”, including restrictions for participants.

“Feel the ViBe” is to be used ad libitum. However, to stimulate participation, participants receive a fact or figure by email or text message every day (Table 1). Elements, such as the guided chat and “facts and figures”, are repeated every twelve weeks. Strictly spoken there is no hard endpoint to the intervention, because “Feel the ViBe” is meant to support participants as long as they need this. However, we decided to link measurements to this twelve week period (Figure 1). Some items are obligatory to fill out to gain access to other features, such as the questionnaires. Restrictions are given in Table 1. “Feel the ViBe” is monitored by a community manager who answers questions, guides the chat, moderates the forum and addresses possible safety issues with participants. To prevent bias, the Community Manager uses a protocol. Every action from the community manager not covered by the protocol will be registered, discussed with the supervising research team, and, if necessary, added to the protocol.

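### The session mood score (ROM) is described as showing a direct effect of the website, but as planned it is an uncontrolled before-after change, possibly seen only in a selected subset of sessions

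*Protocol article*

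**What the plan says.** Under *Secondary outcome measures*, participants grade their mood in a pop-up at each login, and then: "After logging out they will receive a pop-up asking the same question". The stated use is: "The scores and differences in scores before and after the session are analyzed to find any direct effects of visiting the website". The abstract (*Methods/design*) says: "Routine Outcome Measurement (ROM) will be used to measure a direct effect of participating in the intervention".

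Table 1 (*Intervention*) describes the same procedure: "Directly after login and after logout a popup appears to the participant requesting to state their mood". Its only access restriction for ROM is a login. Table 1 also lists an emergency exit, open to all visitors: "A button on every page directing participants to" an outside search page.

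The control condition, described with Figure 1, is a restricted version of the site "offering only access to the user profile, consent forms, digital testament, research information, questionnaires and the" ask-the-expert function. ROM is not on that list. Table 1 says of ask-the-expert that it is the one element controls can use during the trial.

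*Data analysis* tests effectiveness by ANOVA of the primary outcomes (IES and the SCL-90-R subscales) and gives no between-arm analysis of ROM. *Randomization* states that participants cannot be blinded, and that a randomized trial is preferable to a pre-post design for measuring effectiveness.

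**The concern.** The abstract and the methods assign a causal meaning to a difference between two ratings by the same person in the same session. Nothing in the plan separates an effect of the site from other reasons why mood might differ between login and logout. Four such reasons are regression to the mean, if people visit when they feel unusually low or high; the passing of time; expectation in participants who know what they are receiving; and selective recording of the second rating. Randomization does not help, because no contrast between arms is planned for this outcome.

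At stake is what may be concluded from a secondary result. If the plan is followed as worded, a mean rise in mood would count as evidence that visiting the site improves mood, although the design cannot show that.

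**Working it through.** The document gives no ROM sample size, expected effect, standard deviation or missing-data rate, so there is no ROM figure to reproduce. The check has two parts.

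**1. The passages side by side**

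- *Claim:* a direct effect, in both the abstract and *Secondary outcome measures*.
- *Comparator:* none described. The control access list omits ROM, and the ANOVA in *Data analysis* is confined to the primary outcomes.
- *Timing of visits:* chosen by the participant, since *Intervention* says the site is used ad libitum.
- *Rating:* self-reported and unblinded (*Randomization*).
- *Trigger of the second rating:* logging out, in both places that describe it. No other trigger is mentioned.
- *Other ways to leave:* the emergency exit on every page. The document does not say whether using it, closing the browser or timing out brings up the pop-up.

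So the change is uncontrolled, and the sessions with both ratings may not represent all sessions.

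**2. An illustration of size, with assumed inputs only**

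Assume that the site has no effect. Mood has SD 1 and mean 0, and the login-logout correlation r is 0.5, 0.7 or 0.9. Let p be login mood and q logout mood. None of these values comes from the document.

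(a) *Login times selected, all logout scores recorded.* If login mood averages d SD below the usual level, the expected change is (1 − r) × d. With d = 0.5:
- r = 0.5: 0.5 × 0.5 = +0.25 SD
- r = 0.7: 0.3 × 0.5 = +0.15 SD
- r = 0.9: 0.1 × 0.5 = +0.05 SD

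(b) *Login times not selected, logout scores recorded selectively.* Suppose the odds of a recorded second score rise e-fold per SD of logout mood, so that half are recorded. Among recorded sessions the expected change is (1 − r) × E[q | recorded], and numerical integration gives E[q | recorded] = 0.413:
- r = 0.5: 0.5 × 0.413 = +0.21 SD
- r = 0.7: 0.3 × 0.413 = +0.12 SD
- r = 0.9: 0.1 × 0.413 = +0.04 SD

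If the odds instead *fall* e-fold per SD, the same values appear with a minus sign.

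(c) *Both.* With d = 0.5, logout mood has mean −0.5r, and the expected change among recorded sessions is (1 − r) × E[q | recorded] + 0.5 × (1 − r²):
- r = 0.5: 0.5 × 0.206 + 0.375 = +0.48 SD
- r = 0.7: 0.3 × 0.124 + 0.255 = +0.29 SD
- r = 0.9: 0.1 × 0.041 + 0.095 = +0.10 SD

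(d) *Neither.* The expected change is 0.

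A simulation of 400,000 sessions per setting gave the same values to two decimals. Under these assumptions the apparent rise with no true effect therefore runs from 0 to about 0.5 SD, and case (b) shows that the sign can also reverse.

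**The case against.** The best defence is that *direct* here means *immediate*. The rating concerns mood at that moment, Table 1 uses the word in the sense of time ("Directly after login and after logout a popup appears"), and looking for any effects sounds exploratory. The protocol tests effectiveness elsewhere, on the primary outcomes. This lowers the weight of the point but does not remove it, because an immediate effect of visiting the website is still a causal statement.

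Several stronger readings are tempting, and the document does not support them:

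- *That control participants have no ROM data.* Table 1 restricts ROM only by login, and controls do log in, so the pop-up may appear to them. What can be said is that their access list omits ROM and that no comparison between arms is described.
- *That every session ended without logging out lacks a second score, and that these are the worse sessions.* The document does not say what the emergency exit or a closed browser triggers. A hurried exit may reflect who entered the room, not mood.
- *That people log in when they feel low, so mood must rise.* This is not stated. Daily facts and figures, scheduled chats and questionnaire reminders are prompts unrelated to mood.
- *That repeated sessions will be analysed as independent, giving standard errors that are too small.* No ROM model is stated. Following participants from session to session is compatible with a within-person analysis, and the choice of model belongs in a statistical analysis plan.

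The same holds for the method of handling missing logout scores: its absence from a protocol article is no finding. What stands is the causal wording, and a measurement procedure that may record only some sessions in full.

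**Conclusion.** The point holds as a minor one. As described, ROM gives an uncontrolled, self-timed, unblinded change in mood within a session, and that cannot show a direct effect of the website. The protocol's own preference for a randomized trial over a pre-post design argues against that reading. Because logging out is the only described trigger for the second score, the observed differences may also come from a selected subset of sessions. That part is an inference from what the document describes, not something it states.

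The range of 0 to about 0.5 SD rests wholly on the assumed login shift, correlation and recording pattern. It shows that a rise of visible size is possible without any effect; it does not estimate the bias in this trial. The primary analysis, the sample size and the main effectiveness conclusion are untouched.

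**What to change.** In the abstract and under *Secondary outcome measures*, replace the direct-effect wording with *uncontrolled change in mood during a session (descriptive)*. Beside the result, report how many sessions have no logout score and the login mood in those sessions, so that a reader can judge how selected the rest are.

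The cost is a change of wording and a short table, which should need only data that the site already captures. Nothing changes for participants, and adding ROM to the control arm is not required. The downside is a weaker claim for this secondary outcome.
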